### 2.16. Data Management and Confidentiality

Data will be collected on standardized CRFs and managed in a secure electronic data-capture system, such as REDCap, with controlled access, audit trails, and structured validation [27].

Each participant will have a unique study identifier; direct identifiers will be stored separately and access restricted to authorized personnel. Data review will include range/logic checks, missing data queries, and periodic cross-center completeness and consistency checks.

### 2.17. Patient and Public Involvement

Patients and the public were not formally involved in protocol design, conduct, reporting, or dissemination planning. Participant/caregiver feedback may inform operational refinements subject to appropriate review and approval.

### 2.18. Trial Status

The study is registered at ClinicalTrials.gov (NCT07738354), will enroll 300 participants across 15 centers from 1 September to 31 December 2026, and will follow each participant for 6 months. As of 1 August 2026, recruitment had not begun and the registry status was not yet recruiting.

## 3. Expected Results

The study is expected to determine whether the integrated pathway can be delivered consistently across participating settings and to quantify the enrollment, assessment completion, risk-matched intervention delivery, fidelity, follow-up completion, data completeness, and intervention-related adverse events. It will also provide prospective estimates of 6-month toileting-related fall occurrence and within-participant changes in urinary symptoms, nocturia, mobility, balance, and independence in activities of daily living. Because there is no concurrent control group, clinical changes will be interpreted as exploratory and hypothesis-generating rather than evidence of causal effectiveness.

## 4. Discussion

This protocol addresses toileting-related falls as a multidimensional clinical and care-delivery problem rather than as an isolated mobility event. By integrating urinary symptoms, gait and balance, physical function, psychological/cognitive factors, caregiver support, and environmental hazards within one decision pathway, the program is intended to reduce fragmentation between disciplines that commonly manage these risks separately. The approach is particularly relevant to people with disability or care dependency, in whom several modifiable risks may coexist and change over time. Recent longitudinal evidence from residential care also suggests that changes in mobility, supervision, activity, and care conditions can accompany changes in fall occurrence, reinforcing the importance of the care environment when interpreting fall risk [28].

A major strength of the study is its prospective multicenter implementation focus. Standardized assessment, risk stratification, intervention assignment criteria, documentation, training, and quality control procedures are combined with flexibility in the intervention package so that care can be adapted to individual clinical indications and local resources. The RE-AIM-informed evaluation will provide information not only on clinical events and functional changes but also on the reach, adoption, intervention delivery, fidelity, follow-up, data quality, and safety. Together with the center-level implementation measures, these data should help identify which elements of the pathway are reproducible across settings and which require local adaptation.

The study also has important limitations. The absence of a concurrent control group prevents causal attribution of changes in fall outcomes or functional measures to the integrated program. Observed within-participant changes may reflect the intervention, natural recovery or deterioration, regression to the mean, concurrent clinical care, or other time-related factors; clinical outcomes will therefore remain exploratory and hypothesis-generating. Participants will intentionally be heterogeneous in age, disability or functional impairment, comorbidity, urinary symptoms, mobility, care setting, caregiver support, and intervention exposure. The prespecified subgroup analyses will characterize this heterogeneity descriptively rather than confirm differential effects. In addition, participants may receive different combinations and intensities of urinary, rehabilitation, psychological/cognitive, caregiver, and environmental interventions; consequently, any observed clinical change cannot be reliably attributed to a single component of the pathway. Fall ascertainment may remain vulnerable to incomplete reporting despite the monthly structured surveillance, and not all symptom or functional instruments will be applicable to every participant. Variations in staffing, equipment, rehabilitation capacity, case mix, and local service organization may also contribute to inter-center differences in delivery. The common core protocol, standardized training and documentation, uniform surveillance, prespecified assignment criteria, and center-level fidelity monitoring are intended to limit this variability, but the center and center-type findings will remain descriptive rather than confirmatory.

If the integrated pathway demonstrates acceptable implementation, fidelity, safety, and follow-up performance, subsequent research should evaluate its effectiveness using comparative designs, such as pragmatic controlled or cluster-randomized studies and should examine the cost, resource use, sustainability, and the contribution of individual intervention components. The anticipated findings will be relevant to care delivered jointly by urology, rehabilitation medicine, nursing, psychology, geriatrics or primary care and community or long-term care services. Coordinated multidisciplinary implementation is therefore a central feature of the program rather than an ancillary component.

## 5. Conclusions

This multicenter protocol integrates urinary, rehabilitation, psychological/cognitive, caregiver, and environmental management within one toileting-related fall pathway. It will evaluate its implementation and safety while generating prospective clinical estimates to guide later comparative, sustainability, and cost-effectiveness studies.

## Figures and Tables

**Figure 1 healthcare-14-02794-f001:**
[figure not shown]
Overall study flowchart and technical roadmap.

**Table 1 healthcare-14-02794-t001:** Schedule of enrollment, intervention, and follow-up assessments.

Study Activity	Screening/Baseline	Intervention and Dynamic Management (0–6 Months)	Six-Month Assessment
Written informed consent	●		
Eligibility screening	●		
Demographic and medical history	●		
Multidimensional baseline assessment	●		
Risk stratification and individualized care plan	●	Review and adjustment	
Urinary symptom/nocturia management		As indicated	Review
Gait, balance, and physical rehabilitation		As indicated	Review
Psychological/cognitive support		As indicated	Review
Environmental and caregiver intervention		As indicated	Review
Fall and toileting-related fall surveillance		Ongoing	Final verification
Adherence and intervention delivery monitoring		Ongoing	●
Adverse event monitoring		Ongoing	●
OABSS	●		●
Nocturia episodes/voiding record	●	As clinically indicated	●
Tinetti Performance-Oriented Mobility Assessment	●		●
Modified Barthel Index	●		●
Implementation outcome assessment		Ongoing	●

Note: The symbol ● indicates a prespecified assessment or procedure at the corresponding study stage. The intervention components are selected according to individual risk factors and clinical indications; not every participant receives every component. OABSS, Overactive Bladder Symptom Score.

**Table 2 healthcare-14-02794-t002:** Operationalization of the RE-AIM framework in the present study.

RE-AIM Domain	Operational Definition	Prespecified Measures	Data Source/Time Point
Reach	Extent to which eligible individuals enter the integrated care pathway	Enrollment rate: Number enrolled/number of eligible screened individuals; distribution of enrolled participants by recruitment setting and key demographic/clinical characteristics	Screening and enrollment logs; recruitment period
Effectiveness	Exploratory clinical and safety outcomes observed during participation in the pathway	Proportion experiencing ≥1 toileting-related fall; nighttime toileting-related falls; total falls; change in OABSS, nocturia episodes, Tinetti score, and Modified Barthel Index; intervention-related adverse events	Baseline, prospective event surveillance, and Month 6 assessment
Adoption	Uptake of the pathway by participating centers and designated clinical/research personnel	Proportion of participating centers completing study initiation requirements and initiating enrollment; proportion of designated personnel completing standardized protocol training	Center initiation records and training logs; before and during recruitment
Implementation	Extent to which the standardized assessment, intervention assignment, delivery, and documentation procedures are implemented as intended	Completion of clinically applicable baseline assessments; proportion receiving risk-matched intervention; risk–intervention concordance; protocol fidelity/deviation rate; intervention documentation; required data completeness	CRFs, intervention records, fidelity records, and coordinating-center review; baseline through Month 6
Maintenance	Continued participation in and use of the pathway during the prespecified 6-month study period	Participant 6-month follow-up completion rate; proportion of centers continuing protocol-based follow-up and pathway delivery for enrolled participants through completion of the study follow-up period	Follow-up records and center implementation records; Month 6

**Table 3 healthcare-14-02794-t003:** Multidimensional risk assessment, intervention, and outcome matrix.

Risk Domain	Core Assessment	Potential Intervention Components	Prespecified Outcomes
Urinary function	OABSS; urinary frequency; urgency; nocturia; urinary incontinence; voiding difficulty; voiding diary; clinically indicated PVR and Qmax	Behavioral and bladder training; fluid and voiding management; scheduled toileting; clinically indicated medication optimization; neuromodulation or electrical stimulation when appropriate	Toileting-related falls; nighttime toileting-related falls; OABSS; nocturia episodes
Gait, balance, and physical function	Muscle strength and tone; joint mobility; sit-to-stand and transfer ability; gait; balance; Tinetti assessment; mobility aids	Balance and gait training; strength and endurance training; transfer training; assistive device adaptation; rehabilitation therapy	Total falls; Tinetti score; Modified Barthel Index
Psychological and cognitive factors	Fear of falling; anxiety; depressive symptoms; cognition; fall-related psychological responses; treatment cooperation; caregiver support	Psychological support; behavioral strategies; cognitive training; reminders; caregiver education and structured assistance	Adherence; functional independence; fall occurrence; clinically relevant symptom change
Environment and care	Nighttime lighting; bed-to-toilet route; slippery surfaces; thresholds; handrails; toilet height; bedside facilities; caregiver response	Environmental modification; handrails and night lighting; non-slip measures; bedside toileting devices; assisted or scheduled toileting; care-process optimization	Environmental risk correction; safe toileting; toileting-related falls

**Table 4 healthcare-14-02794-t004:** TIDieR-informed specification of core intervention domains.

Intervention Domain	Core Components	Provider/Setting	Planned Dose Specification	Tailoring/Progression	Exposure/Fidelity
Urinary	Fluid/voiding education; bladder training; scheduled voiding; medication review; neuromodulation/electrical stimulation if indicated	Urology/clinical team; participating care setting	Frequency/schedule; session/device parameters when applicable; intended duration	Adjust to symptoms, response, safety, and goals	Initiation, adherence/exposure, modifications, non-delivery and reason
Rehabilitation	Strength, balance, gait, transfer, and endurance training; mobility aid adaptation	Rehabilitation or appropriately trained clinical staff	Frequency; session duration; intervention period; initial intensity/assistance	Progress, reduce, or modify by function, tolerance, response, and safety	Sessions/exposure, adherence, modifications and reasons
Psychological/cognitive	Psychological support; behavioral strategies; cognitive training; reminders	Appropriately trained clinical staff	Planned frequency and duration of contacts/training	Adapt to cognition, psychological status, cooperation, and function	Delivery, adherence when applicable, and major modifications
Caregiver	Education; transfer/toileting assistance; scheduled toileting; supervision	Study staff with participant caregiver	Training contacts; assistance/supervision schedule	Adapt to dependency, toileting pattern, cognition, and caregiver capacity	Training/delivery, adherence, and changes
Environmental	Lighting; route; handrails; non-slip measures; toilet height/bedside device adaptation	Multidisciplinary team, caregiver, or local service personnel	Required modification(s) and implementation timing	Match identified hazards, safety, and feasibility	Completion/non-completion and reason

**Table 5 healthcare-14-02794-t005:** Prespecified clinical, implementation, and safety outcomes.

Outcome Category	Outcome Measure	Time Frame
Primary	The 6-month cumulative incidence of at least one toileting-related fall	Up to 6 months after enrollment
Secondary	Number of nighttime toileting-related falls	Up to 6 months after enrollment
Secondary	Total number of falls from any cause	Up to 6 months after enrollment
Secondary	Change in OABSS	Baseline and Month 6
Secondary	Change in average nocturia episodes per night	Baseline and Month 6
Secondary	Change in Tinetti Performance-Oriented Mobility Assessment score	Baseline and Month 6
Secondary	Change in Modified Barthel Index	Baseline and Month 6
Reach	Enrollment rate among eligible screened individuals	At completion of recruitment
Adoption	Proportion of participating centers completing study initiation requirements and initiating participant enrollment	During the recruitment period
Adoption	Proportion of designated study personnel completing standardized protocol training	Before participation in study assessment or intervention delivery
Implementation	Completion rate of protocol-required and clinically applicable multidimensional baseline assessments	At baseline
Implementation	Proportion of participants receiving at least one documented individualized intervention matched to identified risk factors and clinical indications	Up to 6 months after enrollment
Implementation	Risk–intervention concordance rate	During the 0–6-month intervention period
Implementation	Proportion of participants with ≥1 predefined intervention fidelity deviation	Up to 6 months after enrollment
Implementation	Completeness of protocol-required study data	At Month 6
Maintenance	Six-month participant follow-up completion rate	At Month 6
Maintenance	Proportion of participating centers continuing protocol-based pathway delivery and follow-up for enrolled participants through completion of the 6-month study period	At completion of the 6-month study follow-up period
Safety	Proportion experiencing intervention-related or possibly related adverse events	Up to 6 months after initiation of intervention

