### 2.8. Risk Stratification and Intervention Assignment

After the baseline assessment, the multidisciplinary team will identify the clinically relevant and modifiable risks and assign one or more of five intervention domains: urinary, mobility/physical, psychological/cognitive, caregiver, and environmental. Each assignment requires a documented corresponding risk that materially contributes to toileting exposure, unsafe transfer or mobility, or fall risk; is potentially modifiable within the program; and has no clinical contraindication to the proposed intervention.

The domain-level assignment criteria will be standardized across centers, and assignment to one domain will not preclude simultaneous intervention in others. The specific modality, intensity, frequency, duration, and combinations may be tailored to symptom severity, functional capacity, safety, participant goals and preferences, caregiver capacity, and local resources. The planned intervention parameters and subsequent major modifications will be documented prospectively.

Urinary care will target symptoms that drive urgent, frequent, or nighttime toileting; rehabilitation will target deficits in strength, transfer, gait, balance, endurance, or mobility aid use; psychological/cognitive care will target factors that impair safe toileting or adherence; caregiver interventions will address assistance, supervision, or knowledge gaps; and environmental interventions will target modifiable hazards such as lighting, route obstacles, slippery surfaces, handrails, toilet height, and bedside facilities.

The CRF will document the identified risk factor, assigned intervention domain, selected component, clinical rationale, and subsequent modifications. When a potentially indicated component is not delivered because of contraindication, participant preference, caregiver limitation, or resource constraint, the reason will also be recorded. This documentation will support assessment of intervention exposure and risk–intervention concordance.

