### 2.10. Training, Intervention Standardization, Fidelity Assessment, and Quality Assurance

Before implementation, the relevant staff will receive standardized training on eligibility assessment, multidimensional evaluation, risk stratification, intervention assignment and principles, device use when applicable, data collection, confidentiality, and safety reporting. Common manuals, CRFs, and intervention assignment checklists will be used across centers, and training completion will be documented for the personnel involved in assessment or intervention delivery.

Participant-level fidelity will assess completion of protocol-required and clinically applicable baseline assessments; documentation of identified risks and assigned domains; concordance between risks and assigned interventions; initiation of planned interventions or a documented reason for non-delivery; major modifications and their reasons; and completion of required follow-up and safety documentation. Concordance will quantify both whether assigned domains are supported by documented baseline risks and whether clinically relevant risks receive an intervention or a documented reason for non-delivery.

Center-level implementation consistency will be evaluated using assessment completion, risk–intervention concordance, intervention delivery and documentation, adherence to monthly fall surveillance, follow-up completion, data completeness, and protocol deviations. Indicators will be summarized separately for each center and, where informative, by center type.

The coordinating center will review these indicators periodically. Recurrent deficiencies will trigger clarification, targeted retraining, and corrective feedback while preserving the common core protocol and documentation standards.

Fidelity deviations will include unjustified omission of required assessment, intervention assignment without documented indication, omission of indicated intervention without explanation, or failure to document a major care plan modification.

Quality control will cover process fidelity, data quality, and safety through standardized CRFs, range/logic and missing data checks, staff competency and equipment checks, adverse event documentation, and escalation procedures.

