### 2.11. Follow-Up, Fall Ascertainment, and Dynamic Adjustment

Participants will be followed for 6 months using a standardized fall surveillance schedule across all centers, with structured contacts at Months 1, 2, 3, 4, and 5 and a final assessment at Month 6. Contacts may be conducted in person, by telephone, or by video according to accessibility; however, the surveillance interval, core questions, fall definitions, and event documentation procedures will be identical across centers. Additional clinical contacts may occur according to need but will not replace the scheduled surveillance.

The 6-month period was selected a priori to balance clinically meaningful prospective observation with feasibility in a multicenter implementation study. It permits estimation of 6-month toileting-related fall occurrence together with short-term changes in urinary symptoms, nocturia, mobility, functional independence, fidelity, safety, and follow-up performance. The monthly structured surveillance is intended to reduce recall-related underreporting; the study is not designed to establish long-term preventive effectiveness, recurrent fall risk beyond follow-up, or long-term organizational sustainability.

At enrollment, participants and/or caregivers will be instructed to record and promptly report any fall during follow-up. At each monthly contact, investigators will use a standardized surveillance form to determine whether a fall occurred since the previous contact and will document the date; relationship to going to, using, transferring on or off, or returning from the toilet; nighttime occurrence; location and circumstances; resulting injury; and assistance available at the time.

A fall is an event in which a participant unintentionally comes to rest on the ground, floor, or another lower level. Toileting-related falls will use the prespecified primary outcome definition. Caregivers may assist in reporting when participants cannot report reliably. Events reported between scheduled contacts will be reconciled at the next contact to avoid duplication.

Missed monthly contacts will be completed as soon as feasible and documented. At Month 6, all fall records will undergo a final completeness and classification review.

Care plans may be modified for new risks, symptom change, poor adherence, adverse events, or changes in function or care environment; major modifications and reasons will be documented.

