#### 2.12.3. Prespecified RE-AIM Implementation and Safety Outcomes

Reach: Enrollment rate among eligible screened individuals at completion of recruitment.Adoption: Proportion of centers completing initiation requirements and starting enrollment.Adoption: Proportion of designated personnel completing standardized protocol training before study procedures.Implementation: Completion rate of required and clinically applicable baseline assessments.Implementation: Proportion receiving ≥1 documented risk-matched individualized intervention during follow-up.Implementation: Risk–intervention concordance and predefined fidelity deviation frequency during follow-up.Implementation: Completeness of required baseline, intervention, and follow-up data at Month 6.Maintenance: Participant 6-month follow-up completion rate.Maintenance: Proportion of centers continuing protocol-based pathway delivery and follow-up through the 6-month study period.Safety: Proportion experiencing ≥1 adverse event judged as related or possibly related to a study intervention during follow-up.

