Potential center effects will be examined explicitly. The primary cumulative incidence estimate and key implementation outcomes will first be reported for the overall cohort, with center-specific estimates and confidence intervals presented descriptively. When a clustering adjustment is required, the center will be incorporated as a random intercept if a stable estimation is possible. If not, it will be included as a fixed categorical effect where feasible; otherwise, center-specific descriptive estimates will be used. The center findings will characterize implementation heterogeneity and will not be formal rankings of institutional performance.

The implementation and fidelity indicators will also be summarized by center type to characterize the variation across levels of care, without inferring differential effectiveness.

Exploratory multivariable models will use covariates prespecified a priori on clinical grounds rather than data-driven stepwise selection: age, sex, baseline fall history, comorbidity burden, baseline functional status, caregiver support, recruitment setting, baseline urinary symptom status, and predominant disability/functional impairment profile. Model complexity will be limited according to sample size and available event counts to reduce overfitting; participating centers will be included as a random intercept when stable estimation is possible.

Prespecified subgroup analyses will examine age (18–64 vs. ≥65 years), predominant impairment profile (physical/mobility, cognitive, or mixed/multidomain), recruitment setting, baseline urinary symptoms, and functional dependency. Subgroup estimates will include 95% confidence intervals; regression-based heterogeneity analyses will be exploratory when data permit, with no claims of differential effectiveness.

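### The fidelity-deviation outcome is worded three ways, and its Table 5 form ignores how often a participant could deviate, so the center-type summary can mix case complexity with fidelity

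*Protocol article*

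**What the plan says.** The protocol article describes this outcome in three places.

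- Table 5: "Proportion of participants with ≥1 predefined intervention fidelity deviation", a yes/no measure per participant.
- Section 2.12.3: "Risk–intervention concordance and predefined fidelity deviation frequency during follow-up".
- Table 2, Implementation row: "protocol fidelity/deviation rate", with no denominator.

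Section 2.10 says what counts: "Fidelity deviations will include unjustified omission of required assessment, intervention assignment without documented indication, omission of indicated intervention without explanation". The same sentence adds one more, namely a substantial change to the plan of care that goes unrecorded. That makes four deviation types.

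The number of chances to deviate is not fixed. Under Section 2.7 some instruments are given only where they apply. Under Section 2.8 the team will "assign one or more of five intervention domains: urinary, mobility/physical, psychological/cognitive, caregiver, and environmental". Under Section 2.11, "Care plans may be modified for new risks, symptom change, poor adherence, adverse events, or changes in function or care environment".

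Section 2.15 adds: "The implementation and fidelity indicators will also be summarized by center type to characterize the variation across levels of care". Section 2.1 expects case mix to vary between settings. The hypothesis in Section 2.2 is consistent implementation across levels of care, judged by the RE-AIM and fidelity measures.

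**The concern.** The three wordings can give different numbers from the same records. A proportion of participants, a count and a rate are different quantities, and the rate has no stated denominator.

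The one operational form, in Table 5, scores a participant with one deviation the same as a participant with six. It also gives someone with many applicable steps more chances to be counted than someone with few. If one level of care enrolls more complex participants, its figure will tend to be higher even when staff are equally faithful at each step. A real difference in fidelity can likewise be masked by an opposite difference in complexity.

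This touches the study's central question, because fidelity measures are what the consistency hypothesis rests on. Section 2.10 also has the coordinating center review center-level indicators, including protocol deviations, and retrain where deficiencies recur. A center could draw attention for its case mix and not its practice.

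**Working it through.** **The plan's own figures.** The article computes nothing for this outcome. Its only calculations are the precision figures in Section 2.14. These reproduce as 1.96 × √(0.25/n): 5.66, 5.96, 6.14 and 6.33 points for n = 300, 270, 255 and 240, against the stated 5.7, 6.0, 6.1 and 6.3. They do not bear on the definition of the outcome.

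**Inputs from the article.** Four deviation types (Section 2.10); one to five domains per participant (Section 2.8); an unfixed number of modifications (Section 2.11).

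**Assumptions, not in the article.**
- The deviation probability per step, q, is 1%, 2% or 5%, and is the same for everyone.
- The number of steps is k = 1 (assessment) + 2 × domains + modifications. One domain with no modification gives k = 1 + 2 + 0 = 3. Five domains with three modifications gives k = 1 + 10 + 3 = 14.

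**Independent steps.** P(at least one deviation) = 1 − (1 − q)^k.

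| q | k = 3 | k = 14 |
|---|---|---|
| 1% | 3.0% | 13.1% |
| 2% | 5.9% | 24.6% |
| 5% | 14.3% | 51.2% |

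Deviations divided by steps would equal q in both columns.

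**One chance per domain instead of two.** Then k runs from 1 + 1 + 0 = 2 to 1 + 5 + 3 = 9. At q = 5% this gives 1 − 0.95² = 9.8% and 1 − 0.95⁹ = 37.0%. The gap is smaller but has the same direction.

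**Correlated steps.** Deviations may cluster within a participant. A beta-binomial model with q = 5% gives:

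| Correlation | k = 3 | k = 14 |
|---|---|---|
| 0.05 | 13.6% | 42.1% |
| 0.2 | 11.8% | 27.8% |
| 0.5 | 8.9% | 15.2% |

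The gap shrinks but closes only if deviations within a participant are completely dependent.

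**Overlapping case mixes.** Take two center types, both with q = 5% and independent steps. One has 50/30/15/5% of participants at k = 3/6/8/14; the other has 10/20/40/30%. The probabilities at those k are 14.3%, 26.5%, 33.7% and 51.2%. The weighted results are 22.7% and 35.6%, at identical fidelity per step.

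**Masking.** With q = 2% and k = 14, the outcome is 1 − 0.98¹⁴ = 24.6%. The same 24.6% arises at k = 3 when q = 1 − (1 − 0.246)^(1/3) = 9.0%.

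**Coverage by other Table 5 outcomes.**

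| Deviation type (Section 2.10) | Other outcome that addresses it |
|---|---|
| Omitted required assessment | Completion of applicable baseline assessments |
| Assignment without documented indication | Risk–intervention concordance |
| Unexplained omission of an indicated intervention | Risk–intervention concordance |
| Undocumented major modification | None specific to it |

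**The case against.** The strongest reply is that Table 5 does not leave fidelity to this one measure. Assessment completion is restricted to applicable assessments. Concordance, as described in Section 2.10, looks both at whether assignments are supported by risks and at whether risks are acted on or explained. Section 2.10 reads center consistency from seven indicators, of which protocol deviations is one. Sections 2.15 and 4 call center findings descriptive, rule out rankings and name case mix as a source of differences. No threshold depends on the outcome. All of this stands and limits the consequence. It does not make the three wordings agree, and a descriptive figure still needs to be interpretable.

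A reader might infer that the study will misreport consistency across levels of care. The documents do not support that. They give no per-step rates, no step counts by level of care and no within-participant correlation, and they do not say which level has the more complex participants.

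A reader might also infer that centers using the pathway more fully are penalized. That is only partly so. More identified risks, domains and modifications do add opportunities. But unjustified omission of an assessment and unexplained omission of indicated care are themselves deviations, so full assessment and full delivery lower the measure. Early dropout matters little for baseline assessment and initial assignment, which come first.

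Finally, an at-least-one proportion is a legitimate and readable summary, and preferring another as the sole measure would be partly taste. A fuller definition may also exist in a document not shown. That would not remove the differing wording in this article.

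**Conclusion.** The point holds in limited form. The article names one outcome in three ways, and the form it defines depends on the number of opportunities as well as on fidelity. At equal per-step fidelity it is higher for participants with more applicable steps, unless their deviations are completely dependent. The center-type summary of this indicator can therefore mix complexity with fidelity.

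The size is not known. In the illustrations at 5% per step, the contrast between the simplest and most complex participant ranges from about 6 points (15.2 − 8.9 = 6.3, correlation 0.5) to about 37 points (51.2 − 14.3 = 36.9, independent steps). The more realistic overlapping mixes differ by about 13 points (35.6 − 22.7 = 12.9) under independence. All of these rest on assumed rates and step counts. The gap is least covered for undocumented major modifications, which have no outcome of their own. It is worth correcting because the indicator serves the study's stated hypothesis, but it does not undermine the implementation evaluation as a whole.

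**What to change.** - Use one definition of the outcome in Table 5, Section 2.12.3 and Table 2.
- Keep the proportion of participants with at least one deviation, and report beside it the number of deviations per applicable opportunity.
- Give this separately for the four deviation types, each with its own denominator: required and applicable assessments, assigned domains, indicated interventions, and major modifications. Separate denominators avoid counting twice a domain that is both indicated and assigned.
- Report overall, by center and by center type, with confidence intervals that allow for clustering within participants and centers. With four, five and six centers per type, the center-type intervals should be read cautiously.
- At minimum, stratify the at-least-one proportion by number of assigned domains.

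The cost is a wording change in three places and a little more analysis. Under Sections 2.7 and 2.8 the records already hold non-administration of instruments, identified risks, assigned domains, reasons for non-delivery and modifications. Section 2.18 states that recruitment had not begun by 1 August 2026. The downside is that undocumented modifications can be counted, in numerator or denominator, only when review finds them, so that component will be understated.
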